#### Collection of information after volunteers are enrolled in this study

Some general and basic information will be collected using a structured questionnaire upon patient enrolment, including weight, height, age, gender, birthplace, residence, education level, religious beliefs, and income levels. In addition, the clinical manifestations of every individual will be collected, including fatigue, night sweats, chest tightness, chest pain, dyspnea, insomnia, weight loss, and loss of appetite. The structured questionnaire will also be used to collect information that may considerably affect treatment efficacy and outcomes. These factors include smoking and alcohol consumption, socio-economic patterns such as floating population and tramp, working conditions (such as exposure to dust, high temperature, and high humidity), and conditions affecting the lungs (silicosis, pneumoconiosis, tuberculosis). Other factors include the use of antibiotics, and debilitating conditions such as HIV/AIDS, hepatitis B, COPD, hyperthyroidism, hypertension, nervous system diseases (disorders, abnormalities), hyperuricemia, cardiovascular diseases (including coronary heart disease), lung cancer, and tumors, among others.

The treatment information for COVID-19 will also constitute a key influencing factor to explore the efficacy of the treatment in this study. The key information will include weight (before and after treatment), SARS-CoV-2 infection time, diagnosis time, length of the hospital stay, and pulmonary infections caused by other pathogens. Furthermore, the use of antibiotics, plasma therapy, alpha interferon, lopinavir/ritonavir, ribavirin, nasal catheter oxygen inhalation, mask oxygen inhalation, invasive mechanical ventilation, extracorporeal membrane oxygenation (ECMO), immunosuppressants, corticosteroids, and TCM, we also recorded.

#### Information collection from participants during each follow-up

Each subject enrolled in the study will be followed-up once every 3 months and the described indices will be determined each time. A total of 5 (months 0, 3, 6, 9, and 12) determinations per subject will be made during the study period.

In each follow-up, a structured questionnaire will be used to collect clinical information and indices. These included cough, expectoration, fatigue, chest tightness, chest pain, dyspnea, insomnia, emaciation, loss of appetite, VC, TLC, FVC, FVC%, DLCO, DLCO%, FEV1, RV, MVV, RV/TCL, ERV, IRV, PEF, MMEF, VT, IC, 6-min walking distance, Borg dyspnea score, and TCM syndrome scores, which are reflective of respiratory function and will help determine TCM syndrome scores. Moreover, the SCL-90, SF-36, SAS, and SDS scales will be used to record and measure quality of life for each individual during every follow-up.

### Statistical analysis

#### Database

The database will be generated using EpiData 3.1 (The EpiData Association, Odense, Denmark) and all data will be recorded by two operators and tested for consistency. Three databases will be established, including a full analysis set (FAS), per protocol set (PPS), and safety set (SS). The total number of selected and completed cases in each study center will be shown and the number of dropouts and the reasons will also be listed.

#### Principles of data analysis

Statistical analysis will be performed using the SAS Analytics Software Solutions (version 9.4, SAS Institute Inc., Cary, North Carolina 27,513, US). Odds ratio (OR) and 95% confidence interval (*CI*) of categorical variables will be calculated using two-tailed Chi-square test, and Fisher’s exact test will be used to compare the differences in qualitative variables between the two groups. Quantitative variables will be described as the mean, median, standard deviation, or inter-quartile range, and analyzed using the rank-sum test, t-test, analysis of variance (ANOVA), repeated measurement ANOVA, generalized linear mixed model (GLMM), and generalized estimation equation (GEE). Differences will be considered significant at *P* < 0.05 with two-tailed test.

This study will be conducted across several research centers; some subjects from the same center, it may produce similarity or homogeneity. The methods that will be considered for adjusting for effects of the center will include the Breslow-Day method, Cochran-Mantel–Haenszel statistics (CMH), and logistical regression, whereas GEE and GLMM will be used for data mining. In addition, confounding factors will be considered in all data analysis, it will include gender, age, and other lung diseases.

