### Randomization and blinding

The double-blind method will be used for all aspects of this study including the enrolment of participants, investigators, care providers, outcome assessors, and data analysts. A statistician labelled and distributed the study drugs to each site. A study coordinator will be blinded and participants will be assigned in a 1:1 ratio to treatment groups based on the SAS Analytics Software Solutions (version 9.4, SAS Institute Inc., Cary, North Carolina 27,513, US), it will be used to generate random codes using the stratified randomization method. The study center will be the stratification factor. Pharmacists at the pharmacies of all sites of the clinical trial will be blinded to the patient characteristics and will distribute drugs to the patients according to the instructions of the investigators. The selected block length and random initial value seed parameters will be considered confidential data.

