#### Data analysis of secondary efficacy indices

For each subject from the treatment and control groups, the quantitative indicators of respiratory function (TLC, VC, DLCO, FVC, FVC%, VT, IC, 6-min walking distance, and Borg dyspnea score) will be collected several times and GLMM will be performed to determine the effectiveness of therapeutic modalities in a continuous time frame (0, 3, 6, 9, and 12 months).

The treatment effect in TCM syndrome includes clinical cure, notable effect, effectiveness, and ineffective. The clinical cure, notable effect, and effectiveness will be merged into a new variable named “total effective”. Hence, the treatment effect in TCM syndrome will comprise two new dichotomous variables, the qualitative variables, namely, “total effective” and “ineffective,” and will be recorded in each subject when they consult a physician across the time points in the study (0, 3, 6, 9, and 12 months). Hence, GEE will be conducted to determine the efficacy of treatment between the two groups.

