#### Data analysis of quality of life

The SCL-90, SF-36, SAS scale, and SDS scales will be used to measure the quality of life of subjects in both groups when each of the patients will visit a study center during the continuous time points of the study (0, 3, 6, 9, and 12 months). All data are quantitative and GLMM will be conducted to explore the differences in indices between the two groups.

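### Randomisation is stratified by centre, but the GLMM and GEE comparisons of secondary and quality-of-life outcomes do not name centre, so their standard errors may be somewhat too wide

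*Protocol article*

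**What the plan says.** Under Randomization and blinding, "participants will be assigned in a 1:1 ratio to treatment groups", and "The study center will be the stratification factor". No other stratification factor is given.

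The Principles of data analysis section gives the reason to care about centre: "some subjects from the same center, it may produce similarity or homogeneity". It then lists methods for centre effects, and divides them from two others in the same sentence: "Breslow-Day method, Cochran-Mantel–Haenszel statistics (CMH), and logistical regression, whereas GEE and GLMM will be used for data mining". The next sentence adds that "confounding factors will be considered in all data analysis, it will include gender, age, and other lung diseases". Centre is not in that list.

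The outcome sections then assign methods:

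- **Primary outcome (binary):** Breslow-Day, CMH, GEE and logistic regression.
- **Quantitative respiratory outcomes:** "GLMM will be performed to determine the effectiveness of therapeutic modalities in a continuous time frame (0, 3, 6, 9, and 12 months").
- **TCM-syndrome response (binary, repeated):** GEE, to compare the two groups.
- **Quality-of-life scales:** "All data are quantitative and GLMM will be conducted to explore the differences in indices between the two groups".

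None of the three secondary and quality-of-life analyses mentions centre.

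**The concern.** When allocation is balanced within centres, differences between centres largely cancel out of the comparison of arms. A model without centre does not credit this. It leaves the between-centre variance in the error term and reports a standard error larger than the real sampling variation of the treatment estimate. Confidence intervals are then too wide, the test runs below its nominal 5%, and power may be lost. A subject random effect does not repair this for an average difference between arms, because the centre variance is simply absorbed into the between-subject variance.

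The text goes further than silence. It recognises the centre problem, assigns it to three methods that the plan otherwise applies to a categorical outcome, and uses a contrasting conjunction to give GEE and GLMM a different purpose. It then relies on GEE and GLMM for between-arm efficacy comparisons, which are not data mining. So the Principles section conflicts with the three outcome sections on what these models are for, and no analysis of a quantitative outcome is tied to the randomisation stratum.

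Breslow-Day is also misplaced in that list. It tests whether the odds ratio is the same across centres; it does not adjust the treatment effect for centre.

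**Working it through.** **Is there a figure in the plan to reproduce?** Not on this point. The article gives no intra-centre correlation, no number of centres and no power for secondary outcomes. Its sample size is for the binary primary outcome. With the stated inputs, 2 × (2.92 / 0.134)² × 0.533 × 0.467 = 236.4 per group, within 3% of the printed 233. That figure does not bear on centre effects.

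**Inputs**

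- 1:1 allocation stratified by centre (Randomization and blinding).
- Two-sided 0.05 (Principles of data analysis), critical value 1.96.
- Reference power of 80% with centre in the model. This is a yardstick only, since no power is stated for these outcomes.
- R, the share of outcome variance lying between centres (the intra-centre correlation). This is an assumption, run from 0.01 to 0.20.

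**Formulas, for a comparison of means**

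With arms balanced within centres, the true variance of the difference is (1 − R) times the variance reported by a model without centre. Hence:

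- Standard error ratio = 1 / √(1 − R)
- Actual two-sided type I error = 2 × [1 − Φ(1.96 / √(1 − R))]
- Power without centre = Φ(2.80 − 1.96 / √(1 − R)), where 2.80 = 1.96 + 0.84

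Example at R = 0.10: √0.90 = 0.9487, so the ratio is 1.054. The effective critical value is 1.96 × 1.054 = 2.066, and power is Φ(2.80 − 2.066), about 76.9%.

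| R (assumed) | SE ratio | Type I error | Power if centre omitted |
|---|---|---|---|
| 0.01 | 1.005 | 4.9% | 79.7% |
| 0.02 | 1.010 | 4.8% | 79.4% |
| 0.05 | 1.026 | 4.4% | 78.5% |
| 0.10 | 1.054 | 3.9% | 76.9% |
| 0.20 | 1.118 | 2.8% | 72.9% |

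**Simulation check** (10 equal centres, 460 patients, 3,000 runs; these sizes are also assumptions)

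- R = 0.05: power 78.7% without centre, 79.6% with it.
- R = 0.10: mean standard error 0.0927 without, 0.0884 with; power 77.5% against 80.4%.
- R = 0.20: mean standard error 0.0922 without, 0.0834 with; power 72.7% against 78.9%.

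The simulated standard error ratios (1.049 and 1.106) fall slightly below the formula because, with 10 centres, about 9/10 of R reaches the residual. At R = 0.20 that gives √(0.98 / 0.80) = 1.107.

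**Where the loss vanishes.** If the tested contrast is change from baseline and the centre effect is constant over time, the effect subtracts out. At R = 0.20 the simulated standard error was 0.0834 with and without centre.

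**Where the formula does not carry over.** For the GEE of the binary TCM response with a logit link, leaving centre out also changes what is estimated. The result is an odds ratio averaged over centres, which lies closer to 1 than the odds ratio conditional on centre.

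**The case against.** The strongest reply is that no passage excludes centre from the GLMM or GEE. The secondary-outcome sections list no model terms beyond treatment and time, and they do not repeat age and gender either, although the Principles section applies those to all analyses. Model terms commonly sit in an analysis plan, which is not shown. The lists are also open: methods will be considered, and will include those named. The covariate sentence supplements the one on centre, so centre need not reappear in it. GEE and GLMM are standard tools for clustered data, and the awkward clause could be a loose way of saying so.

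Much of this stands. A reader might infer that the plan deliberately drops centre from these models, that it has only binary-outcome methods for centre, and that power is therefore lost. The documents do not support that reading. Nothing forbids a centre term. Generalised CMH can handle ordered scores. The Principles section also lists the rank-sum test, t-test, ANOVA and repeated-measures ANOVA for quantitative variables, so GLMM is not the only method named. Any loss depends on an unstated correlation and on which contrast is tested, which the article does not fix.

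The reply does not remove the conflict. An analysis plan that put centre into the GLMM for centre adjustment would have to override the division of methods that the protocol states.

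**Conclusion.** The point holds as a wording conflict with a possible, modest loss of precision. As written, the comparisons of secondary and quality-of-life outcomes are not tied to the one factor used to stratify randomisation, and the stated role of GEE and GLMM contradicts their use.

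The size rests on the assumed correlation. For a comparison of means, the cost is about 1.5 power points or less at 0.05 or below, about 3 points at 0.10 and about 7 points at 0.20. It is nil for a change contrast with a stable centre effect.

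The error is conservative, so it does not create false positives, and it concerns outcomes with no stated power. The primary outcome is not affected in this way, since CMH and logistic regression, which the plan links to centre, are named for it.

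**What to change.** - In Principles of data analysis, delete the clause that reserves GEE and GLMM for data mining, and add centre to the adjustment terms.
- In the sections on secondary efficacy indices and quality of life, state that every between-arm GLMM includes centre, as a fixed effect or as a random intercept if there are many small centres, alongside the subject effect.
- State that the GEE for the total-effective TCM response includes centre as a covariate, and that its odds ratio is then conditional on centre.
- Describe Breslow-Day as a test of homogeneity of odds ratios across centres, not as an adjustment for centre.

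The cost is text only. Drug supply, enrolment and case counts are already organised by centre, so no patients, visits or measurements are added. The models spend a few degrees of freedom, and very small centres may need a pooling rule. Making the change before the data are seen also removes a later discretionary choice about centre.

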
##### Exclusion criteria

Patients who meet any of the following exclusion criteria will be excluded from this trial. First, diagnosis of any lung diseases, such as bronchiectasis, tuberculosis, bronchial asthma, chronic obstructive pulmonary disease (COPD), dyspnea, respiratory failure, lung cancer, or those with a history of these diseases. Second, patients with a status of acute exacerbation of pulmonary fibrosis. Third, patients with severe disorders of the cardiovascular system, nervous system, and digestive system; serious mental diseases, tumors, human immunodeficiency virus (HIV) infection/acquired immune deficiency syndrome (AIDS), tuberculosis, autoimmune diseases, and severe liver and kidney dysfunction. Fourth, patients who received glucocorticoids, immunosuppressants, and other drugs for treatment of pulmonary fibrosis or other diseases in the past 3 months. Fifth, participation in another interventional clinical trial within the past 3 months. Sixth, patients who did not provide informed consent. Finally, lactating women will be excluded from the study.

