#### Secondary outcome measure

*(1) Indices reflecting respiratory function*

Certain variables will be monitored for each subject during every follow-up, including VC, TLC, FVC, FVC%, DLCO, DLCO%, FEV1, RV, MVV, RV/TCL, ERV, IRV, PEF, MMEF, VT, and IC.*(2) Six-minute walking distance and Borg dyspnea score*

The quantitative variable of 6-min walking distance and the Borg dyspnea score will be obtained for each subject in each observation.*(3) Quality of life assessment indices*

The SCL-90, SF-36, SAS, and SDS scales will be used to collect the score (quantitative variable) for each subject during each visit.*(4) Evaluation standard of treatment effect in TCM syndrome*

The treatment effect in TCM syndrome will be divided into four categories based on the guiding principles for clinical research of the new TCM (Trial) (2018 year). The categorical variables are clinical cure, notable effect, effective, and ineffective. The specific classification criteria are as follows:

Clinical cure: a reduction rate of TCM syndrome scores ≥ 95%;

Notable effect: a reduction rate of TCM syndrome scores to between 70 and 95%.

Effective: a reduction rate of TCM syndrome scores to between 30 and 70%.

Ineffective: a reduction rate of TCM syndrome scores < 30%.

The reduction rate of TCM syndrome scores(%) = (pre-treatment TCM syndrome scores-post-treatment TCM syndrome scores) / TCM syndrome scores × 100%

The total effective rate(%) = (clinical cure cases + notable effect cases + effective cases) / total cases × 100%.

The data will be analyzed to determine if there are significant differences between the treatment and control groups after treatment, if there are significant differences in the treatment group pre- and post-treatment, and if there are significant differences in the control group pre- and post-treatment.

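### Month 0 is listed as a visit for the GEE on TCM response although nobody can respond then, and the named adjustment factors include an excluded condition but not baseline lung function

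*Protocol article*

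**What the plan says.** All references are to the Protocol article.

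- **TCM response.** Under *Secondary outcome measure*, the reduction rate is computed as "pre-treatment TCM syndrome scores-post-treatment TCM syndrome scores) / TCM syndrome scores × 100" per cent. The lowest class is "Ineffective: a reduction rate of TCM syndrome scores" below 30%. *Data analysis of secondary efficacy indices* merges the other three classes into one responder category, records the resulting binary variable "across the time points in the study (0, 3, 6, 9, and 12 months"), and on that basis specifies GEE.
- **Mixed models.** For the respiratory indices, 6-minute walk and Borg score, "GLMM will be performed to determine the effectiveness of therapeutic modalities in a continuous time frame (0, 3, 6, 9, and 12 months"). The quality-of-life scales are analysed by GLMM "during the continuous time points of the study (0, 3, 6, 9, and 12 months"). Neither section names the treatment term to be tested.
- **Adjustment factors.** *Principles of data analysis*: "confounding factors will be considered in all data analysis, it will include gender, age, and other lung diseases".
- **Eligibility and data collection.** *Exclusion criteria* rule out "diagnosis of any lung diseases, such as bronchiectasis, tuberculosis, bronchial asthma" and further named conditions, and also a history of them. The section on information collected after enrolment still gathers silicosis, pneumoconiosis, tuberculosis, COPD and lung cancer. VC, TLC, DLCO and the TCM score are all scheduled at month 0.

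**The concern.** The GEE visit list conflicts with the definition of the outcome. A response defined as change from pre-treatment cannot occur at the pre-treatment visit, so month 0 holds no information on treatment. Depending on how visit enters the model, the fit breaks down or the reported odds ratio is pulled towards 1.

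The adjustment list has a related weakness. One of its three named factors should not vary among eligible subjects. The baseline measurements most directly tied to the outcomes are absent from it, although entry admits FVC% from 50 to 90% and DLCO from 30 to 90%. At stake are the size of the reported TCM effect and the precision of the adjusted analyses.

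**Working it through.** **Inputs.** The plan gives no response rate for the TCM outcome, so there is no figure of its own to reproduce on this point. For illustration I borrow the two rates under *Sample size calculation*, 0.767 (treatment) and 0.533 (control), and assume they hold at each of months 3, 6, 9 and 12. The sample size is not affected.

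**1. Response at month 0.** Pre-treatment minus current score is 0, so the reduction rate is 0%, which is below 30%. Every subject in both arms is classed ineffective: 0% vs 0%.

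**2. What this does to the GEE.**
- *Treatment-by-visit terms including month 0:* the month-0 odds are 0 in both arms, so the log odds ratio is undefined.
- *Categorical visit plus one treatment effect:* the month-0 intercept diverges, and the visit adds nothing except numerical instability.
- *One treatment effect, no visit terms:* month 0 is averaged in.

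For the last case, with complete data:
- Months 3–12 only: OR = (0.767/0.233) / (0.533/0.467) = 3.292/1.141 = 2.88. Risk difference 0.234.
- With month 0: rates are 4/5 × 0.767 = 0.614 and 4/5 × 0.533 = 0.426. OR = (0.6136/0.3864) / (0.4264/0.5736) = 1.588/0.743 = 2.14. Risk difference 0.187.
- Ratio of log odds ratios: ln 2.14 / ln 2.88 = 0.759/1.059 = 0.72, so the log OR is 28% smaller.

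A simulation with 233 per arm, 60 replicates and an independence working correlation gave 2.14 with month 0 and 2.91 without it.

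The distortion is in the estimate. Each subject's five-visit mean is exactly 4/5 of the four-visit mean, so on the risk-difference scale the estimate and its standard error shrink together and their ratio is unchanged.

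**3. The mixed models.** Suppose, as one possibility, that a single treatment main effect is averaged over all five visits and the true effect is constant from month 3. The estimate is (0 + 1 + 1 + 1 + 1)/5 = 0.80 of the truth. With exchangeable correlation ρ (assumed; the plan gives none), the relative z statistics are:
- all five visits: 0.80 / √[(1 + 4ρ)/5]
- months 3–12 only: 1 / √[(1 + 3ρ)/4]
- months 3–12 adjusted for baseline: 1 / √[(1 + 3ρ)/4 − ρ²]

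| ρ | Five visits | Months 3–12 | Months 3–12, baseline-adjusted |
|---|---|---|---|
| 0.5 | 1.03 | 1.26 | 1.63 |
| 0.7 | 0.92 | 1.14 | 1.87 |
| 0.8 | 0.87 | 1.09 | 2.18 |

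A group-by-time contrast, or a model with baseline means constrained equal, has no such dilution.

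**4. Adjustment factors.** Set side by side, the exclusion of other lung diseases and the naming of other lung diseases as a factor leave a covariate that varies only through protocol deviations. The primary classes compare TLC or VC, DLCO, SaO2 and PaO2 with pre-treatment values, yet no baseline value of these is named.

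**The case against.** - **Month 0 is a legitimate response in a mixed model.** This stands. Constrained-baseline models and group-by-time contrasts use it that way and thereby adjust for baseline. A reader might infer that the GLMM results will be diluted. The plan specifies no main-effect-only model, so the factor 0.80 is conditional.
- **The GEE defect concerns a secondary outcome.** This stands. *Data analysis of the main outcome measure* lists GEE but gives no visits, so nothing shows month 0 entering the primary analysis.
- **The covariate list may be open-ended, and details may sit in an SAP not shown.** This is fair, and it softens the point about missing baseline values. It does not excuse naming a factor that eligibility removes.
- **Omitting baseline does no harm to validity.** Correct: randomisation protects the comparison, and the loss is precision. A reader might expect a marked gain in power for the primary test, but the documents do not support a figure. Any gain depends on an assumed effect size and an assumed baseline association. At the planning rates with about 231 completers per arm (0.9 × 257), z = 0.234 / √[(0.767 × 0.233 + 0.533 × 0.467)/231] = 5.44, so a two-sided 5% test of no difference already has power above 99.9%.
- **A constant covariate drops out of any model.** True. The issue is the contradiction and the slot it occupies.

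**Conclusion.** The concern holds in a limited form. Listing month 0 in the TCM-response GEE is an error of definition that can be read from the text alone. Its illustrative size is an odds ratio of 2.14 instead of 2.88. That assumes the borrowed primary-outcome rates, a constant effect from month 3, complete data and no visit terms. With a month-0 term the consequence is non-estimability instead of dilution.

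The adjustment list conflicts with eligibility and leaves out baseline lung function. The consequence is lost precision, of a size the documents do not allow one to fix, and no bias. For the mixed models the fault is only that the contrast is not named. The point is worth correcting because the changes are specific and nearly free.

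**What to change.** 1. **TCM-response GEE:** use months 3, 6, 9 and 12 as outcome visits, with the month-0 TCM score as covariate.
2. **GLMMs (respiratory indices and quality of life):** test a stated treatment-by-visit contrast, such as month 12. Either take months 3–12 as responses with the month-0 value as covariate, or keep month 0 as a response with baseline means constrained equal.
3. **Primary logistic model:** replace other lung diseases with month-0 values of the lung-function components, for example VC or TLC, and DLCO. Keep age, sex and centre.
4. **Consistency:** reconcile *Exclusion criteria*, the post-enrolment data-collection list and *Principles of data analysis* on other lung diseases.

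The cost is analysis wording only. The month-0 measurements are already scheduled, and neither the visits nor the sample size changes.
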